#### Secondary objectives

##### Aims 2 and 3

In order to study changes over time (ie, evolution of maternal mental health) in the scores obtained on the self-report questionnaires (SCL-90-R, STAI-Y, CISS, PCL-5, EPDS) completed by the mother and to study changes as a function of medical, sociodemographic and lifestyle factors, a linear mixed model will be applied. This model takes into account the random effect induced by the analysis of three repeated measurements. The cofactors tested (fixed effects) will be the variables likely to influence the scores on these self-report questionnaires (medical, sociodemographic and lifestyle). The results of the linear mixed model are expressed for each factor in the form of a coefficient corresponding to the variation brought about by this factor on the basal score (intercept). A positive coefficient indicates a score-raising effect, while a negative coefficient indicates a score-lowering effect. For the time effect, the coefficient reflects the variation during the follow-up, while for the other factors, the estimate reflects the variation induced by the presence of the factor. The interactions between the co-factors and time will also be tested. A similar methodology will be applied for each score.

##### Aim 4

We will use a structural equation model to estimate simultaneously the relationships among maternal mental health (as captured by SCL-90-R, STAI-Y, CISS, PCL-5 and EPDS scores), prenatal factors (medical, sociodemographic and psychological) and child development (Bayley-4 and ASQ-3).

The structural pathways linking these three latent constructs, whereby maternal mental health impacts prenatal factors, which in turn influence the child’s development, while also allowing for a residual direct effect of maternal mental health on developmental outcomes.

We will quantify the mediating role of each block of prenatal factors by estimating the proportion of the effect of maternal mental health on child development that is transmitted through those factors. The model will be fitted using robust maximum likelihood estimation, with bootstrapping to derive CIs for indirect effects.

##### Aim 5

The GSI of the SCL-90-R will be used as an indicator of co-parent mental health. It is a standardised score with a T-score (mean 50, SD 10). The Bayley-4 cognitive score will be used as an indicator of neurodevelopment in children with CHD at age 1. This is an exploratory analysis, independent of the primary outcome.

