#### Secondary objectives

*Aim 2*: To describe the evolution of maternal mental health (ie, anxiety, depression and psychological adjustment scores), from the antenatal period to the neonatal postoperative period (after cardiac surgery), and finally when the child with CHD turns 1 year. We predict that maternal psychological distress will decrease over time, as we expect that the most acute period of stress will be closest to the initial diagnosis of fetal CHD (T1, T2 and T3).

*Aim 3*: To identify the medical and sociodemographic factors associated with prenatal maternal psychological distress of women carrying a fetus diagnosed with cyanotic CHD. We hypothesise that lower maternal educational attainment and poor family support as well as fetal factors such as diagnosis of severe CHD (ie, univentricular heart) will be associated with worse prenatal maternal mental health outcomes (ie, overall mental health, anxiety and depression symptoms). The evaluation of scores obtained on self-report questionnaires (SCL-90-R,^29^ State-Trait Anxiety Inventory (STAI-Y),^31^ Coping Inventory for Stressful Situations (CISS),^32^ Edinburgh Postnatal Depression Scale (EPDS),^33 34^ Posttraumatic Stress Disorder Checklist for DSM-5 (PCL-5)^35 36^) completed by the mother will be analysed in relation to medical, sociodemographic and lifestyle factors.

*Aim 4*: To explore the mediating role of prenatal risk factors (ie, medical factors and maternal coping strategies, such as task-oriented, avoidant and emotional coping) in the association of prenatal maternal mental health (ie, distress, anxiety and depression) and neurodevelopment in children with CHD. We will also explore the potential interaction effects between sociodemographic factors and mental health on neurodevelopment in CHD. We hypothesise that expecting mothers with low socioeconomic levels of support and/or with maladaptive coping strategies (eg, avoidant, emotional reactivity) will experience the greatest effects of prenatal distress on their children’s neurodevelopmental outcomes at 1 year of age. The mediating role of medical and psychological antenatal factors (information extracted from the medical record, the interview and the information questionnaire) on the relationship between maternal mental health scores (SCL-90-R, STAI-Y, CISS, EDPS, PCL-5) and the child’s neurodevelopment (Bayley-4,^30^ Ages and Stages Questionnaire-Third Edition (ASQ-3)^37^) will be characterised.

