### Procedures

The inclusion visit at Time 0 will take place at each participating centre during the usual follow-up fetal congenital cardiology consultation after the initial diagnosis of cyanotic CHD. The investigator will inform the participant, answering all questions concerning the aims, the nature of the constraints, the foreseeable risks and the expected benefits of the research.

Figure 1 indicates the study visit collection. At Time 1 (third trimester of pregnancy) after obtaining agreement to participate and signing written consent, a semi-structured psychological interview, lasting about 45 min will be conducted. Three main themes will be investigated: (1) diagnosis of CHD, experience of pregnancy and mental health (ie, post-diagnosis psychological experience, existing family resources); (2) perspectives and projections (ie, how to imagine one’s life after one’s child’s heart surgery) and (3) expectancies towards a maternal mental health intervention in the context of prenatal CHD diagnosis. The prenatal psychological interviews may be conducted on site at each centre before or after a follow-up clinical consultation, or by telehealth in order to facilitate the participation of expectant mothers in the study. Self-report questionnaires assessing psychological state (SCL-90-R), anxiety (STAI-Y) and coping strategies (CISS), as well as an information questionnaire (sociodemographic aspects and lifestyle) will be collected. This information questionnaire will collect information about level of education, employment status, marital status, family situation (living alone or with others, number of children), geographical area of residence and distance between home and maternity hospital, available resources (type of support that can be requested and obtained, whether practical, financial or emotional), lifestyle habits, including smoking, alcohol and drugs, physical activity and sleep quality. The questionnaires take approximately 30 min to complete. The time required to complete all the questionnaires is estimated at around 30 min for the mother and 30 min for the father or co-parent. The total duration of the visit is estimated at between 45 min and 1 hour 15 min for the mothers and 30 min for the co-parent. Participants have the possibility to complete the questionnaires at home, after receiving the instructions.

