**Figure 1 F1:**
[figure not shown]
Study visit and data collection schedule. CHD, congenital heart disease; GA, gestational age.

At Time 2 (after surgery, before the child is discharged from hospital), a post-partum depression questionnaire (EPDS), an anxiety questionnaire (STAI-Y) and a coping scale (CISS) will be administered to the participants, at the most convenient time for them. Finally, an information note concerning the child’s next visit will be given to the parents along with parental consent for the child’s participation.

At Time 3, a follow-up consultation will be conducted with mothers and their 12 to 18 months old child. The mother will be offered a psychological state questionnaire (SCL-90-R), an anxiety scale (STAI-Y), a coping scale (CISS) and a post-traumatic stress scale (PCL-5). A neurodevelopmental examination using the standardised ASQ-3 and Bayley-4 tests will be conducted, including an assessment of the child’s behavioural and socio-emotional development, and their neurodevelopment (cognition, language, fine and gross motor skills, as well as psychosocial development). No measures will be collected for the co-parent at Time 3. Figure 2 summarises the measurements.

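### The three-measurement mixed model planned for all five maternal questionnaires does not match the visit text, and cannot be fitted to EPDS or PCL-5

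*Protocol article*

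**What the plan says.** The data analysis plan for Aims 2 and 3 names all five maternal instruments as outcomes of one longitudinal model: "scores obtained on the self-report questionnaires (SCL-90-R, STAI-Y, CISS, PCL-5, EPDS) completed by the mother and to study changes". It states the data structure, "This model takes into account the random effect induced by the analysis of three repeated measurements", adds that "The interactions between the co-factors and time will also be tested", and extends the approach to every instrument: "A similar methodology will be applied for each score".

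The Procedures section sets out what the mother completes at each visit:

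- T1 (third trimester): "Self-report questionnaires assessing psychological state (SCL-90-R), anxiety (STAI-Y) and coping strategies (CISS"), plus the information questionnaire.
- T2 (after surgery, before discharge): "a post-partum depression questionnaire (EPDS), an anxiety questionnaire (STAI-Y) and a coping scale (CISS) will be administered to the participants".
- T3 (12 to 18 months): "a psychological state questionnaire (SCL-90-R), an anxiety scale (STAI-Y), a coping scale (CISS) and a post-traumatic stress scale (PCL-5").

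Aim 2 promises a course over three periods, the last being the child's first year, for several constructs ("ie, anxiety, depression and psychological adjustment scores), from the antenatal period to the neonatal postoperative period"), and predicts that distress falls across T1, T2 and T3. Aim 3 concerns factors associated with prenatal distress, depressive symptoms included, and lists EPDS and PCL-5 among the scores to be analysed.

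**The concern.** The analysis section assumes three values per mother on each of five instruments, and the visit text does not provide them. This is not a detail that a fuller analysis plan could supply, because no later document can model visits at which the instrument was not given. At stake are two secondary aims. Aim 2's statement about depression over time would rest on an EPDS score with a single time point. Part of Aim 3 would rest on instruments that, according to the visit text, are first given after birth. If the visit text rather than the analysis section is wrong, the risk is greater: prenatal EPDS values not collected in pregnancy are lost.

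**Working it through.** **Step 1. Count administrations from the Procedures section.**

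| Instrument | T1 | T2 | T3 | Visits |
|---|---|---|---|---|
| STAI-Y | yes | yes | yes | 3 |
| CISS | yes | yes | yes | 3 |
| SCL-90-R | yes | no | yes | 2 |
| EPDS | no | yes | no | 1 |
| PCL-5 | no | no | yes | 1 |

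The plan's own figure, three measurements per score, is reproduced for 2 of the 5 instruments.

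**Step 2. Write the stated model.** For mother i at visit j, before adding covariates:

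y_ij = β0 + β1·[visit = T2] + β2·[visit = T3] + b_i + e_ij, with covariance matrix per mother V = σ_b²·J + σ_e²·I,

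where J is the all-ones matrix and I the identity, both of size equal to the number of visits. Estimability needs rank 3 for the fixed part (intercept and two visit contrasts) and rank 2 for the pair (J, I), so that the two variance components can be told apart.

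**Step 3. Check the ranks under the schedule in Step 1.**

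| Instrument | Fixed part (3 needed) | Variance part (2 needed) | Consequence |
|---|---|---|---|
| STAI-Y | 3 | 2 | estimable as stated |
| CISS | 3 | 2 | estimable as stated |
| SCL-90-R | 2 | 2 | random intercept and T1-T3 contrast; no T2 effect |
| EPDS | 1 | 1 | not estimable as stated |
| PCL-5 | 1 | 1 | not estimable as stated |

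With one visit, J and I are both the number 1, so V = σ_b² + σ_e² and only the sum is identified. Visit is constant across all mothers, so the time effect is confounded with the intercept, and each factor-by-time term is confounded with the factor itself.

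This does not depend on treating visit as categorical. With time as a single linear term the fixed part needs rank 2. SCL-90-R then reaches 2, its slope being the T1-T3 difference rescaled, while EPDS and PCL-5 remain at 1.

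**Step 4. Set the aims against the counts.**

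- Aim 2, anxiety: three points on STAI-Y.
- Aim 2, depression: one point on EPDS (T2). The Primary outcome measures section lists depression among the SCL-90-R dimensions, which gives two further points (T1 and T3) on a different instrument. No single measure of depression covers all three visits.
- Aim 2, overall distress: two points on SCL-90-R, none after surgery.
- Aim 3, prenatal scores: SCL-90-R, STAI-Y and CISS exist at T1. EPDS and PCL-5 do not.

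**The case against.** Several arguments limit the point.

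- **SCL-90-R can be modelled.** This is correct. Two visits support a mixed model with a T1-T3 contrast, so the instruments to which the model truly cannot be fitted number 2 of 5, not 3.
- **There is some longitudinal information on depression.** This is also correct. A reader might infer that no depression trajectory exists at all, but the SCL-90-R depression dimension is available at T1 and T3. What is missing is a three-point course and any repeat of EPDS.
- **Aim 3 can be answered from the mixed model.** A reader might infer that factor coefficients would average over postnatal visits and so miss the prenatal association. That holds only for a model without factor-by-time terms. The plan describes coefficients relative to a basal score and says time interactions will be tested. With T1 as reference visit and those interactions included, a factor's main effect is its T1 association. The real conflict in Aim 3 is its listing of EPDS and PCL-5.
- **The share of Aim 2 that is answerable is uncertain.** A reader might infer that only one of its three named constructs has three time points. The protocol does not tie psychological adjustment to an instrument; if it means coping on CISS, the count is two of three. Depression falls short on either reading.
- **The visit text may be the incomplete part.** Figures 1 and 2 were not available for this review. The abstract says expecting women report on depression, and Aim 3 links EPDS and PCL-5 to prenatal outcomes. If the figures show further administrations, they disagree with the Procedures text, so reconciliation is still needed. It remains open which passage should change.
- **A similar methodology need not mean an identical model.** With one visit, the fixed part reduces to ordinary regression. That is a sensible analysis, but it describes no change over time, which is what the section sets out to study.

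**Conclusion.** The contradiction stands. On the visit text as written, the stated model can be fitted in full to STAI-Y and CISS, in reduced two-visit form to SCL-90-R, and not at all to EPDS or PCL-5. Aim 2's depression course over T1, T2 and T3 is not estimable, and Aim 3 names two instruments with no scheduled prenatal administration. The conclusion rests on the Procedures text being complete, which could not be checked against Figure 1; if that text is incomplete, the inconsistency remains and the correction moves to the visit text. The primary analysis uses only the T1 SCL-90-R score and the Bayley-4 cognitive score and is untouched, and nothing here depends on the sample size.

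**What to change.** First reconcile the secondary objectives, the Procedures text and the analysis section for Aims 2 and 3 with the visit schedule in Figure 1.

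If the visit text is right:

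- Use the three-visit mixed model for STAI-Y and CISS only, with visit as a categorical effect.
- Use a T1-T3 model for SCL-90-R (GSI and depression dimension).
- Analyse EPDS at T2 and PCL-5 at T3 by single-time regression on the chosen factors, with no time terms.
- Answer Aim 3 from T1 scores, or from an explicit T1 contrast in the mixed model, for SCL-90-R, STAI-Y and CISS only.
- Reword Aims 2 and 3 to match.

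These are changes of wording and cost nothing in data collection.

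If EPDS is meant to be measured prenatally or followed over time, correct the visit text before recruitment. This costs an amendment and 10 items at each added visit. The article gives June 2025 as the start, so the decision is urgent: a T1 score missed in pregnancy cannot be obtained afterwards.

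### Aim 3 asks about prenatal distress, but its mixed-model coefficient is not tied to the prenatal visit, and two of its listed questionnaires have no prenatal score

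*Protocol article*

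**What the plan says.** **The question.** Under Aims and hypotheses, Secondary objectives, Aim 3 is "To identify the medical and sociodemographic factors associated with prenatal maternal psychological distress of women carrying a fetus diagnosed with cyanotic CHD". Its hypothesis links lower education, poor family support and a univentricular heart to "worse prenatal maternal mental health outcomes (ie, overall mental health, anxiety and depression symptoms"). The same paragraph lists five maternal questionnaires for this aim: SCL-90-R, STAI-Y, CISS, EPDS and PCL-5.

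**The analysis.** The Data analysis plan treats Aims 2 and 3 together with one linear mixed model per score: "This model takes into account the random effect induced by the analysis of three repeated measurements". Results for each factor are given "in the form of a coefficient corresponding to the variation brought about by this factor on the basal score (intercept"). Then, "for the other factors, the estimate reflects the variation induced by the presence of the factor". Finally, "The interactions between the co-factors and time will also be tested".

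**The visits.** Procedures gives the T1 set as "Self-report questionnaires assessing psychological state (SCL-90-R), anxiety (STAI-Y) and coping strategies (CISS"), plus an information questionnaire. T2 has EPDS, STAI-Y and CISS. At T3, "The mother will be offered a psychological state questionnaire (SCL-90-R), an anxiety scale (STAI-Y), a coping scale (CISS") and PCL-5.

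**The concern.** Aim 3 concerns a level at one visit, during pregnancy. The model stated for it is built to describe change over visits, and no sentence in the plan ties a factor's coefficient to the prenatal visit.

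If the model is read by its main effects, an association that arises only after birth can be reported as a determinant of prenatal distress. A univentricular heart, for example, might raise maternal scores after surgery through a harder postnatal course. Conversely, a factor that acts only before birth is diluted. The Introduction wants these determinants for risk stratification, so the visit to which the association belongs matters.

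There is a second mismatch. Two of the five questionnaires listed for Aim 3 are not given before birth, so they cannot answer the question under any model.

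**Working it through.** The plan states no figure on this point to reproduce. The check compares the question with the model and the visit schedule, then illustrates the size.

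**Step 1: which scores exist at which visit** (text of Procedures; the two figures are not visible in the copy reviewed).

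| Questionnaire | T1 | T2 | T3 | What a main-effect coefficient averages |
|---|---|---|---|---|
| STAI-Y, CISS | yes | yes | yes | T1, T2, T3 |
| SCL-90-R | yes | no | yes | T1, T3 |
| EPDS | no | yes | no | nothing: one postnatal score |
| PCL-5 | no | no | yes | nothing: one postnatal score |

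Three repeated measurements therefore exist only for STAI-Y and CISS. For EPDS and PCL-5 a repeated-measures model cannot be fitted, and any factor coefficient is wholly postnatal.

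**Step 2: what the coefficient estimates.** Take a factor that is constant over visits, complete data, a random intercept and no factor-by-time term. The factor's coefficient is then the plain mean of its visit-specific effects:

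- effects 0/5/5 at T1/T2/T3: (0+5+5)/3 = 3.3, though the prenatal effect is 0
- effects 0/5 at T1/T3 (SCL-90-R pattern): (0+5)/2 = 2.5, though the prenatal effect is 0
- effects 5/0/0: (5+0+0)/3 = 1.7, though the prenatal effect is 5

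With factor-by-time terms kept and T1 as reference, the factor coefficient is the T1 effect: 0, 0 and 5.

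**Step 3: how often this would mislead.** From the documents: 87 dyads, and SD 10 (the GSI T-score). Assumed: factor prevalence 50%, within-mother correlation 0.5 (variance 50 between mothers and 50 within), no attrition, two-sided 5% test. The variance of a difference between the two factor groups is the per-mother variance times 4/87.

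- Mean of three visits: SE = √[(50 + 50/3) × 4/87] = 1.75
- Mean of two visits: SE = √[(50 + 50/2) × 4/87] = 1.86
- T1 alone: SE = √[100 × 4/87] = 2.14

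Chance of a significant result, normal approximation:

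- 0/5/5, averaged coefficient: 3.33/1.75 = 1.90, about 48%
- 0/5, averaged coefficient: 2.5/1.86 = 1.35, about 27%
- 5/0/0, averaged coefficient: 1.67/1.75 = 0.95, about 16%; T1-specific coefficient: 5/2.14 = 2.33, about 65%

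A 200-run simulation of the same settings gave mean averaged coefficients of 3.6, 2.4 and 1.95, significant in 56%, 24% and 20% of runs, and 70% for the T1-specific coefficient. The pattern is the same. The gaps reflect the small number of runs, so the closed-form figures are the ones to use.

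**Step 4: is the interaction test a safeguard?** For a 5-point difference between the T1 and T3 effects, assume 70 dyads (87 × 0.8 = 69.6) and SD 10, with p the factor prevalence and ρ the within-mother correlation:

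SE = 10 × √[2(1−ρ)] × √[1/(70p) + 1/(70(1−p))]

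- p = 0.20, ρ = 0.4: SE 3.27, power 33%
- p = 0.33, ρ = 0.5: SE 2.54, power 50%
- p = 0.50, ρ = 0.6: SE 2.14, power 65%

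If non-significant interactions were dropped, the averaged coefficient would often stand even when the effects differ by visit.

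**The case against.** The best defence is that the plan leaves room for the right analysis. It describes the coefficient as a shift in the basal score, and it plans factor-by-time interactions. With time coded from T1 and those interactions in the model, the coefficient is the prenatal effect. Nothing says that non-significant interactions will be removed, and a reference visit or a retention rule is the kind of detail that a fuller document may hold.

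Much of this stands. A reader might infer that the plan has fixed a pooled, wrong parameter for Aim 3. The text does not support that: averaging is what happens without retained interactions, and the article does not say which form is final. Nor may one infer that every score is pooled over three visits, since SCL-90-R, the main distress measure, has no postoperative score. It would also be too strong to say that a postnatal effect would confirm the Aim 3 hypothesis: on the assumptions above the false signal reaches significance in roughly a quarter to a half of studies. The 0/5/5 and 5/0/0 patterns are deliberately extreme.

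What the defence does not remove is this. In a main-effects model the shift of the intercept is the same at every visit, so the reference to the basal score does not by itself make the coefficient prenatal. The plan goes beyond silence, since it names the model for Aim 3 and says how to read its coefficient, and that reading names no visit. The EPDS and PCL-5 mismatch depends on no modelling choice.

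**Conclusion.** The point holds in a conditional form. The Aim 3 question and the coefficient reported for it are not tied together. Unless factor-by-time terms are retained with T1 as reference, the coefficient is an average over T1 and postnatal visits: three visits for STAI-Y and CISS, two for SCL-90-R. A postnatal-only effect of 5 points would then be reported as 3.3 or 2.5, and a prenatal-only effect of 5 as 1.7 for the three-visit scores.

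These averages assume complete data, a random intercept and a factor that does not change over visits; dropout would shift the weights. The significance rates and the 33–65% interaction power also rest on the assumed prevalences and correlations, which the documents do not give.

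For EPDS and PCL-5 the conclusion is unconditional, going by the text of Procedures: with no prenatal score and only one visit each, they cannot inform Aim 3 and cannot enter the stated model.

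The primary analysis uses the prenatal SCL-90-R score directly and is not affected.

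**What to change.** 1. State a separate analysis for Aim 3: a linear regression of each T1 score on the medical, sociodemographic and lifestyle factors. Alternatively, report the T1 factor contrast from a mixed model with T1 as reference that keeps factor-by-visit terms whatever their p-value.
2. Limit Aim 3 to the questionnaires collected at T1: SCL-90-R, STAI-Y and CISS. Prenatal depression would then rest on the SCL-90-R depression dimension, which Primary outcome measures lists among its nine.
3. Keep the visit-averaged coefficients for Aim 2, and label them as such.
4. Reconcile the listing of EPDS and PCL-5 in Aim 3 and in the mixed-model paragraph with the visit schedule in Procedures, and restrict the statement about three repeated measurements to the scores that have them.

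This changes wording and analysis only and needs no new data. The price is precision: on the assumptions above, the T1-specific interval is about 22% wider than the three-visit average (2.14/1.75) and about 15% wider than the two-visit one (2.14/1.86).

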### Secondary outcome measures

Secondary outcomes will be specific anxiety symptoms (STAI-Y), coping skills (CISS questionnaire), depression (EPDS questionnaire) in relation to neurodevelopmental and behavioural scores.

The STAI-Y^31^ is a 40-item self-report questionnaire assessing trait anxiety (20 items) and state anxiety (20 items). Each item is rated on a four-point Likert scale, from 1 (= almost never) to 4 (= almost always), with higher scores indicating greater anxiety.The CISS^32^ is a 48-item self-report questionnaire assessing individual coping styles in response to stress. It evaluates three primary coping dimensions: task-oriented coping, emotion-oriented coping and avoidance-oriented coping. Each item is rated on a five-point Likert scale, from 1 (= not at all) to 5 (= very much), with higher scores indicating greater use of the coping style.The PCL-5^35 36^ is a 20-item self-report questionnaire assessing symptoms of PTSD as defined by the DSM-5. Symptom severity is evaluated across four clusters, namely: intrusion, avoidance, negative alterations in cognition and mood and arousal and reactivity. Each symptom is rated on a five-point Likert scale, from 0 (= not at all) to 4 (= extremely), depending on its severity in the last month. A score above the cut-point score of 31–33 indicates PTSD.The EPDS^33 34^ is a 10-item self-report questionnaire assessing postpartum depression symptoms. Each item is rated 0 to 3 depending on the frequency of symptoms in the last week. Total scores range from 0 to 30, with scores above the cut-off point of 12.5 indicating postpartum depression.The ASQ-3^37^ is a parental questionnaire for children aged 1 month to 5 years 6 months that screens five developmental domains: communication, gross motor, fine motor, problem-solving skills and adaptive skills. Each domain contains six items, rated 10 (=yes), 5 (=sometimes) or 0 (= not yet) by the parent or caregiver depending on their child’s current skills. The ASQ-3 is a recommended screening tool of child development with good psychometric properties.^37 41^

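### Aims 3 and 4 concern prenatal maternal mental health, but two of the five scales listed for it (EPDS, PCL-5) are scheduled only after birth

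*Protocol article*

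**What the plan says.** Under Aims and hypotheses, Aim 3 seeks the factors associated with prenatal maternal distress. It specifies the outcomes as "ie, overall mental health, anxiety and depression symptoms", and its list of instruments includes the EPDS and the PCL-5. Aim 4 takes prenatal maternal mental health as the exposure and lists the same five scales.

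The Data analysis plan for Aim 4 repeats them as indicators of "maternal mental health (as captured by SCL-90-R, STAI-Y, CISS, PCL-5 and EPDS scores". It orders the paths from mental health to prenatal factors to child development, and allows a residual direct effect. For Aims 2 and 3 it puts all five scales into a linear mixed model described as handling three repeated measurements.

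The Procedures section sets the schedule:
- T1, third trimester: "Self-report questionnaires assessing psychological state (SCL-90-R), anxiety (STAI-Y) and coping strategies (CISS", plus an information questionnaire.
- T2, after surgery: "a post-partum depression questionnaire (EPDS), an anxiety questionnaire (STAI-Y) and a coping scale (CISS) will be administered to the participants".
- T3, 12 to 18 months: the SCL-90-R, "an anxiety scale (STAI-Y), a coping scale (CISS) and a post-traumatic stress scale (PCL-5". At the same visit, "A neurodevelopmental examination using the standardised ASQ-3 and Bayley-4 tests will be conducted".

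**The concern.** A mediation model can be read causally only if the exposure comes before the mediators and the mediators before the outcome. A depression score taken after delivery and cardiac surgery does not precede prenatal factors. A post-traumatic stress score taken at the developmental examination does not precede its result. If a mother reports more symptoms at T3 because her child is delayed, a latent exposure containing that score is correlated with the outcome even when prenatal distress had no effect. The error runs towards the study's own hypothesis, and the Discussion looks to these results to target prenatal prevention.

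Aim 3 has a different problem. Mental health is the outcome there, and a postnatal score is not a measurement of the prenatal state that the aim names.

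**Working it through.** **Schedule against use** (Procedures; Aims and hypotheses; Data analysis plan)

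| Scale | T1 | T2 | T3 | Listed for prenatal mental health, Aims 3 and 4 |
|---|---|---|---|---|
| SCL-90-R | yes | no | yes | yes |
| STAI-Y | yes | yes | yes | yes |
| CISS | yes | yes | yes | yes |
| EPDS | no | yes | no | yes |
| PCL-5 | no | no | yes | yes |

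Two of the five scales have no prenatal value. Their recall windows do not reach back to pregnancy. For the EPDS, "Each item is rated 0 to 3 depending on the frequency of symptoms in the last week"; the PCL-5 covers the last month (Secondary outcome measures). With one observation per mother, neither scale supports a time effect or a random effect for repeated measurement.

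**How large the distortion could be.** The plan gives no figure to reproduce, so this is an illustration. The only input from the document is the number of dyads: 87 × (1 − 0.20) = 69.6, taken as 69. Everything else is assumed:
- Prenatal distress d has no effect on the child score y.
- Each scale has variance 1 and loads on d: SCL-90-R 0.8, STAI-Y 0.8, CISS 0.7, EPDS 0.6, PCL-5 0.5.
- The child score acts on PCL-5 with coefficient −b, where b = 0.2, 0.3 or 0.4.

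*Equal-weight sum of the five scales.*
- Variance = (Σλ)² + Σ(1 − λ²) = 3.4² + (5 − 2.38) = 14.18, so the SD is 3.766.
- Spurious correlation r = −b / 3.766 = −0.053, −0.080, −0.106.
- Two-sided 5% rejection rate by Fisher's z: Φ(−1.96 + δ) + Φ(−1.96 − δ), with δ = atanh|r| × √66. This gives 7.2%, 9.9%, 13.9%.
- Simulation with 4000 runs at n = 69 gave 7.4%, 10.1%, 14.6%. A second simulation, with loadings of 0.7 for the three T1 scales and n = 72, gave 7.9%, 10.0%, 15.4%.

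*One-factor score, closer to a latent variable.*
- Weights λ/(1 − λ²) = 2.222, 2.222, 1.373, 0.938, 0.667, so PCL-5 carries 9% of the weight rather than 20%.
- Σwλ = 5.412. Variance = 5.412² + 5.412 = 34.70, so the SD is 5.891.
- r = −0.667b / 5.891 = −0.023, −0.034, −0.045, with rejection rates of 5.4%, 5.9%, 6.6%.
- Simulation at n = 69 gave 5.0%, 6.5%, 7.8%.

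*T1 scores only.* No indicator depends on y, so r = 0 and the rate is the nominal 5%. Simulation gave 4.5% to 5.3%.

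None of these is the full structural equation model. They also leave out any path from the perioperative course to both the T2 EPDS and the later child score, so the EPDS contribution is not quantified.

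**The case against.** The strongest reply has four parts.

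*The visits may be named elsewhere.* The analysis plan sentence for Aim 4 does not itself say prenatal, and an article commonly leaves the visit for each indicator to a fuller document. But the objectives do say prenatal for Aim 4, and no analysis plan can supply a T1 EPDS or PCL-5 that was never scheduled. Figures 1 and 2 are not shown, so a T1 entry there cannot be excluded. The visit-by-visit text has none.

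*Most of the exposure is sound.* SCL-90-R, STAI-Y and CISS all have T1 values. This stands. A reader might infer that Aim 4 as a whole cannot be interpreted, but the documents support only that part of its exposure is mistimed.

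*The effect is small under a latent model.* This also stands. An equal-weight composite of only SCL-90-R, STAI-Y and PCL-5 gave false-positive rates of 10%, 17% and 28% in simulation under the same feedback. The protocol plans a latent model with five indicators, so those figures should not be attached to it.

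*Aim 3 is largely intact.* Scores are modelled one at a time, so the EPDS and PCL-5 do not contaminate the other three. The SCL-90-R also has a depression dimension at T1. A reader might extend reverse causation to Aim 3, but mental health is the outcome there. The defect is confined to the two scales.

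A further inference would be that the ASQ-3 must leave the Aim 4 outcome because the mother rates both it and the PCL-5. The article says only that a parent or caregiver completes the ASQ-3, and the Bayley-4 is in the same construct. Removing it is a preference, not a correction.

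**Conclusion.** The plan is wrong as written on this point, for secondary aims. The EPDS and PCL-5 are listed as measures of prenatal mental health although the schedule collects neither before birth. In Aim 4 this lets reverse causation into the direct effect and the mediated proportion. The false-positive rate would be roughly 5-8% for a five-indicator factor score or 7-15% for an equal-weight composite, against about 5% with T1 scores only. These ranges depend on assumed loadings, on a feedback of −0.2 to −0.4 and on 69 dyads. The timing mismatch depends on none of them. In Aim 3 the two scales cannot answer the question asked and do not fit the repeated-measures model.

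This should be corrected, but it does not threaten the study's main result. The primary analysis relates the T1 SCL-90-R to the Bayley-4 and is unaffected, as is the sample size.

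**What to change.** State that the Aim 3 outcomes and the Aim 4 exposure use T1 scores only: the SCL-90-R, including its depression and anxiety dimensions, and the STAI-Y. Include the T1 CISS if coping stays in the exposure construct; Aim 4 also names coping as a mediator, so its role should be stated. Name T1 explicitly, because these scales are repeated later.

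Take the T2 EPDS and T3 PCL-5 out of the prenatal exposure and out of the model for three repeated measurements. Analyse each as a separate postnatal variable measured once.

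The cost is two indicators in the latent exposure, neither of which was prenatal. No visit, questionnaire or sample size changes; only the wording of Aims 3 and 4 and the specification of their models do.
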